## Abstract

**Background:**

Shared decision making (SDM) is recognized as a person-centered approach to improving health care quality and outcomes. Few digital interventions to improve SDM have been tested in child and adolescent mental health (CAMH) settings. One such intervention is Power Up, a mobile phone app for young people (YP), which has shown some evidence of promise that YP who received Power Up reported greater levels of SDM. However, even though parents play a critical role in CAMH care and treatment, they often feel excluded from services.

**Objective:**

This protocol is for a pilot trial to determine the feasibility of a large-scale randomized trial to develop and evaluate a Web app called Power Up for Parents (PUfP) to support parents and promote involvement in CAMH decisions.

**Methods:**

A 2-stage process, consisting of the development stage and pilot-testing stage of the initial PUfP prototype, will be conducted. At the development stage, a qualitative study with parents and clinicians will be conducted. The interviews will aim to capture the experience of making CAMH decisions, preferences for involvement in SDM, and determine situations within which PUfP can be useful. At the pilot-testing stage, up to 90 parents and their clinicians will be invited to participate in the testing of the prototype. Parents will be randomly allocated to receive the intervention or be part of the control group. This study design will allow us to assess the acceptability and usefulness of PUfP in addition to examining the feasibility of a prospective randomized trial. Clinicians’ perceptions of the prototype and how it has influenced parents’ involvement in SDM will also be examined.

**Results:**

Recruitment began in January 2019 and is scheduled to last for 10 months. Interviews and baseline data collection are currently in progress. To date, 11 CAMH sites have been recruited to take part in the study. It is anticipated that data collection will be completed by October 2019.

**Conclusions:**

The lack of parents’ involvement in CAMH care and treatment can lead to higher rates of dropout from care and lower adherence to therapeutic interventions. There are significant benefits to be gained globally if digital SDM interventions are adopted by parents and shown to be successful in CAMH settings.

**Trial Registration:**

ISRCTN Registry ISRCTN39238984; http://www.isrctn.com/ISRCTN39238984

**International Registered Report Identifier (IRRID):**

DERR1-10.2196/14571

## Introduction

### Background

Worldwide, up to 20% of children and adolescents suffer from a disabling mental illness [1,2]. In England alone, 1 in 8 (12.8%) of 5 to 19 year olds have at least one mental health disorder [3]. As a result, families are faced with many decisions, such as how, when, and where to seek help [4]; agreeing on treatment options when more than 1 treatment option is available [5,6]; agreeing on the goals of treatment [7,8]; and agreeing on the diagnostic tests [9]. However, making decisions for young people (YP) with mental health problems can be challenging, as evident by the high levels of disagreement between parents, YP, and clinicians [10-21]. Researchers and practitioners suggest that the implementation of shared decision making (SDM) in child and adolescent mental health services (CAMHS) can be one approach to reduce treatment disagreements [22] and successfully manage the decision-making process that involves balancing multiple perspectives [23,24].

SDM is recognized as a person-centered approach to improving health care quality and outcomes and has been advocated across many health settings, including child and adolescent mental health (CAMH) [23,25,26]. SDM is defined as the communication process that allows service users and service providers to collaborate when making care and treatment decisions [27]. Although there is an increasing demand to include SDM in health care in support of a person-centered approach, attempting to do this in CAMH settings has been met with particular challenges [28].

In adult settings, decisions are *usually* made between the patient and the clinician or, in the case of a triad, the carer is usually another adult. In CAMH settings, the SDM process is unique as it involves a sometimes-complex triad relationship [27,29] between clinicians, children, and parents. Previous studies have mainly focused on the dyad relationships between physicians and patients; therefore, the areas where triad relationships exist have been less understood. When implementing SDM in CAMH, clinicians are forced to moderate highly stressed parents and children and have complex conversations [23].

Researchers highlight common emotional states such as anxiety, distress, sadness, and worry among families involving a child with a mental illness [30-33]. Parents as primary care providers must adopt the responsibilities of caring for a child with mental challenges, which affects their own quality of life [34-36]. Yet, many studies show that parents feel stigmatized and excluded from services [35,37]. Parents feel as if they lack the necessary support from services to help them with supporting their sometimes-unstable child. However, the SDM literature is scarce on whether these emotional factors positively or negatively impact parental decision-making involvement.

As parents are expected to play a critical role in care and treatment, for example, as copatients (family therapy) or as cotherapists (cognitive behavioral therapy), or be the direct focus of the intervention (parent training) [38,39], it is crucial that these parents are involved in the decision-making process. Studies show that involving service users in CAMH care and treatment decisions is associated with improved health outcomes [40] and higher satisfaction with services [41]. Therefore, parents need support to play an active role in the decision-making process.

Improving SDM in CAMH settings can be accomplished when there is an understanding of the factors impacting how parents make or wish to make intervention or care decisions, and when clinicians are able to offer the necessary support for families to be involved in this type of decision making process. SDM includes the notion of a medical encounter as a *meeting of experts*—the physician as an expert in medicine and the patient/parent as an expert in his or her own life, values, and circumstances [42]. British law states that decisions should be made with the child’s best interest at heart [43]. Therefore, the decision needs of parents and children should be addressed to accomplish quality decisions, where the quality of the decision is judged as *good* if there is consistency with the decision maker’s own values and satisfaction with the decisions made while participating in SDM [44].

### Rationale

The prevalence and burden of CAMH on the National Health Service (NHS) is substantial, and supporting large numbers of families at face-to-face sessions can be a challenge [45]; therefore, the use of digital technology can increase access to interventions [46,47]. Mobile technology (ie, mobile phones, tablets, and laptops) use has been on the rise and is estimated to reach 6.1 billion users by 2020 [48]. This offers the opportunity to take advantage of mobile health (mHealth). mHealth is the general term for the use of mobile phones and other wireless technology in clinical practice [49]. Despite the growing number of mHealth apps, the level of awareness and usability of such apps by patients are reported as still relatively low. Nevertheless, the majority of those who use health apps find them to be beneficial and helpful for living a healthier lifestyle [50].

Power Up is an app, co-designed with YP, to empower YP to take an active role in SDM. Power Up has received positive findings, with YP reporting greater levels of SDM after the intervention period [51]. Building on Power Up, this study aims to involve end users in the development of an intervention, called Power Up for Parents (PUfP), to promote SDM and support parents of children and YP accessing CAMHS.

### Research Questions

The primary research aim for this feasibility study is to develop and investigate whether it is feasible and acceptable to conduct a prospective randomized controlled trial (RCT) of an evidence-based mobile app to promote SDM in families accessing CAMHS.

The following research questions will be addressed:

Is PUfP acceptable and useful for parents and health care professionals?What is the eligibility, participant consenting rates, adherence, and engagement rates of participants using PUfP?Are the outcome measures appropriate and acceptable for a prospective RCT?What are the potential barriers and enablers to conducting a prospective RCT?Which data collection procedures are appropriate and acceptable?What is the scope of the pilot data collected from users and nonusers of PUfP?Can the feedback from PUfP users be used to further refine the prototype for the prospective RCT?

## Methods

### Design

This a 2-stage study involving a development stage (stage 1) where the intervention will be user-tested by clinicians and parents, and suggestions will be obtained for usage and upgrading of the prototype. The pilot-testing stage (stage 2) is a 3-arm, cluster randomized pilot trial with parents accessing CAMHS.

### Study Setting

The study team has identified CAMH sites from 18 NHS trusts throughout England. The study team identified and agreed to use 9 London and 9 non-London sites. CAMHS is being used as a broad term for all services that work with children and YP who are experiencing mental health challenges. However, the focus centers around, but is not limited to, specialist CAMHS, where children and YP receive services from a multidisciplinary team that includes psychologists and psychiatrists.

### Intervention: Power Up for Parents

The PUfP app is an amended version of the original Power Up app that supports and promotes SDM in CAMH settings. The original Power Up is a mobile app used by YP to empower and encourage them to take an active role in the decision-making process [52,53].

The development of the PUfP prototype was guided by the Workbook for Developing and Evaluating Patient Decision Aids [54] and the Ottawa Decision Support Framework [55]. The prototype (see Figure 1) was informed by a scoping review of existing parent-targeted SDM interventions used in CAMH. A further systematic review was conducted to inform the content of PUfP. We consulted the National Children’s Bureau Families Research Advisory Group (FRAG) to obtain input on the study design and how to improve the intervention before the study began. A steering committee involving parents with experience of having a child with mental health problems and the digital lead at the Anna Freud National Centre for Children and Families (AFNCCF) also offered input on the design of PUfP. The content will be screened by various parent groups and professionals before being used in the pilot study. The overall structure of the app’s content is as follows.

**Figure 1 figure1:**
[figure not shown]
The home screen.

#### Decision

This is a decision aid that guides users to seek information about treatment options and the benefits and risks of each option, to track decisions, and to record where more information or support is needed. In addition, as this is a triad relationship, users will be prompted to involve others in the decision-making process by seeking preferences from clinicians, child, or other appropriate persons (see Figure 2).

#### Goal

This feature can be used in sessions or between sessions to record and track goals as they are discussed with health care professionals and the child. This will allow users to plan and record any questions or concerns they have so that they can address them at the next session (see Figure 3).

**Figure 2 figure2:**
[figure not shown]
The decision tab.

**Figure 3 figure3:**
[figure not shown]
The goal tab.

#### Journey

This feature allows parents to reflect on their emotions or issues that may be affecting the decision-making process. A parent can decide to share this content with the child and the clinician, and it can be used during and within sessions to keep track of the decision-making journey from user readiness to outcomes. Expectations, experiences, and reflections can all be recorded here using the diary function (see Figure 4).

#### Support

This section will host a tool to allow parents to identify and express views about various stressors affecting the decision-making process. Users will be able to think about things that are stressful and explore ways to manage these. They can track feelings about decisions and explore where additional emotional support is required (see Figure 5).

**Figure 4 figure4:**
[figure not shown]
The journey tab.

**Figure 5 figure5:**
[figure not shown]
The support tab.

**Figure 6 figure6:**
[figure not shown]
The resources tab.

#### Resources

This section includes useful contact details that can signpost users to further support and guidance. Parents can also upload their own resources to help with the decision-making process and include contacts that they find most helpful (see Figure 6).

### Recruitment

#### Clinicians

All clinicians at the selected NHS sites will be invited to an information session where they will receive information about the study and be given the opportunity to further assist in developing the inclusion criteria for parent participants and inform the recruitment process. This will allow interested clinicians to identify themselves to the research team and become early active participants in the trial. Clinicians for the purpose of this study will support the recruitment process by identifying parent participants within their practice and also, as participants themselves, to inform the development of PUfP and provide feedback on its impact.

#### Parents

On the basis of the inclusion/exclusion criteria agreed at the information session, clinicians will strategically scan their patient list and select suitable participants. At a subsequent meeting with the families, clinicians will solicit interest in participation by sharing some information about the aims of the study. If the family expresses interest in taking part, their contact details will be added to the site’s database of potential participants. The key person at the site will supply the researcher with the database of contact details to invite the parents to participate.

Posters will be placed at participating NHS sites, and parents can also voluntarily contact researchers to express interest in participating. Various parent groups will also advertise the study; therefore, parents may also contact researchers without being identified by clinicians. In addition, the research team will visit the selected CAMHS to recruit participants on clinic days. All parents will be screened to ensure they meet the inclusion criteria. The preliminary inclusion/exclusion criteria are given below.

The inclusion criteria included the following:

Over the age of 18 yearsNo known diagnosed mental health issuesAbility to speak and understand EnglishParent of at least one young person (>11 years) attending CAMHS

The exclusion criteria included the following:

Concurrent and/or involvement in other research that is likely to interfere with the interventionParents or guardians in cases where the child/young person is being treated under a section of the Mental Health Act

#### Patient and Public Involvement

Patient and public involvement (PPI) will be conducted throughout the development of PUfP. The opinions and guidance of parent experts and clinicians will be obtained through consultations on the content and the design of the app. We conducted a 3-part consultation session with the FRAG. First, an email consultation round was conducted where the FRAG provided input on the value of PUfP and identified groups of parents that the research team should target for recruitment. Then, the study design and an example of how the intervention might be used were presented to the group. The pros and cons of various modalities for PUfP were discussed along with general thoughts and concerns on the study design. At the final consultation, parents further discussed how service users could use and benefit from the PUfP in practice.

### Procedure and Materials

NHS sites were identified through consultations with supervisors and other researchers at the AFNCCF and University College London (UCL). CAMHS were recruited from across England, and a key contact person was identified at each site. The contact person will circulate information about the study to all clinicians. Then clinicians will be invited to an information session where they will receive further information about the study. The team will then begin to identify suitable participants already accessing their services based on the inclusion/exclusion criteria further developed at this session. This will be a transparent process where clinicians will scan their patient list and select suitable participants.

Clinicians will then inquire if the selected families are interested in the study and add them to the site’s database of interested participants. Each clinician can continue to add names to the database, and the key contact will provide the updated list of interested participants with their respective contact details as new participants are recruited.

In addition, researchers will attend clinics to distribute flyers and recruit onsite volunteer participants. Parent support groups at the CAMHS services will also be approached, and parents will be given the opportunity to volunteer as participants after information about the study is shared. These forms of recruitment will be guided and informed by PPI participants (parent networks) whose expertise is being sourced to inform the recruitment process.

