#### Stage 2 (Pilot-Testing Stage)

The 18 sites identified will be randomly assigned to either control or 1 of the 2 intervention groups. Intervention group 1 (IG1) will receive the prospective version 1 of PUfP, which includes the *Support* and *Resources* features. Intervention group 2 (IG2) will receive version 2 of PUfP without these 2 features. The cluster randomization was completed independently of the research team, using R software guided by the balance algorithm [59]. Participant-level randomization will not be conducted for this study and parents at all selected sites will have a chance to participate in the study. The Standard Protocol Items: Recommendations for Interventional Trials (SPIRIT) diagram (see Table 1) and flow diagram (see Multimedia Appendix 1) illustrates the pathway through the trial, based on the trial protocol (version 1.3, November 14, 2018) approved by the NHS Research Ethics Committee and the Health Research Authority.

Stage 2 involves reinviting previous participants and obtaining informed consent from all the participants. Participants will be identified and recruited in identical ways as in the development stage. Participants will then be assigned to use the prototype and give feedback on usefulness, usability, and acceptability of the intervention. Up to 90 parents, and their respective clinicians, will be invited to participate in this stage with approximately 30 being allocated version 1 of PUfP, another 30 being allocated version 2, and the remaining 30 as the control group, receiving no app but subject to the same battery of questionnaires and treatment as usual. A sample ranging from 10 to 30 per arm should allow for calculations of feasibility and standardized effect sizes that are small to medium [60,61]. Power calculations, based on repeated measures, within – between comparisons among 3 groups for a single measure across two occasions, indicated that a total sample size of 30 would provide a power of 0.8 to detect an effect size of 0.3. Participants will be assigned to an intervention or control group based on the site from which they have been recruited to avoid contamination.

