#### Stage 2 (Pilot-Testing Stage)

##### Participation Numbers

The number of sites that are approached and the number of sites agreeing to take part will be recorded, in addition to the number of participants agreeing to take part in the study. The proportion of participants completing various parts of the study (ie, consent, pretest, intervention, and posttest) will also be recorded. The app usage rates will also be collected using Google Analytics software.

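### Eligibility criteria stay open and clinicians choose parents after sites were allocated, so arms may enrol different parents and the consent rate may be too high for planning

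*Protocol article*

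**What the plan says.** On allocation, the Stage 2 (Pilot-Testing Stage) section under Procedure and Materials says: "The cluster randomization was completed independently of the research team, using R software guided by the balance algorithm". It adds: "Participant-level randomization will not be conducted for this study". Each parent's arm is that of the recruiting site.

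On eligibility, the Recruitment section (Clinicians) invites clinicians to help develop the parent inclusion criteria at an information session. The Parents subsection labels its own list of criteria preliminary. Procedure and Materials then says: "The team will then begin to identify suitable participants already accessing their services based on the inclusion/exclusion criteria further developed at this session".

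On selection, the Parents subsection says that "clinicians will strategically scan their patient list and select suitable participants". Clinicians ask the selected families whether they are interested. Only interested families enter the site's database, which goes to the researcher. Clinicians may keep adding names. Parents can also come forward through posters, parent groups and researcher visits on clinic days. The Stage 2 section states that recruitment works the same way there as in the development stage.

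On the rates wanted, Research Questions asks: "What is the eligibility, participant consenting rates, adherence, and engagement rates of participants using PUfP". Participation Numbers records sites approached and sites agreeing, "in addition to the number of participants agreeing to take part in the study", together with the proportion of participants completing consent and each later step.

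**The concern.** Randomising sites makes the sites comparable. It makes the parents comparable only if entry to the trial within a site does not depend on the site's arm. Here two things remain open after allocation: the definition of an eligible parent, and the choice of which eligible parents are approached. Both lie at least partly with staff at allocated sites, some of whom will work alongside the app.

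The pilot exists mainly to supply planning figures. Under Planned Analysis, the between-group differences, the standard deviations and the intraclass correlation of the shared decision-making measure feed the sample size of the later RCT. Selective choice of parents could narrow the standard deviation, and criteria that varied between sites could raise the intraclass correlation. A consent rate taken only from parents who passed two earlier filters would make recruitment to the RCT look easier than it is.

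**Working it through.** The plan gives no figure for this point. Its power statement (30 in total, power 0.8, effect size 0.3) can be reproduced if alpha 0.05 and a correlation of 0.5 between occasions are assumed: noncentrality 0.3² × 30 × 2 / (1 − 0.5) = 10.8 on 2 and 27 degrees of freedom gives power 0.800. It has no bearing on who is enrolled.

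**Step 1: order of events.** The Stage 2 section uses two tenses. One sentence reads "The 18 sites identified will be randomly assigned to either control or 1 of the 2 intervention groups"; a later one says that "The cluster randomization was completed independently of the research team". The Results section reports baseline collection under way and 11 sites recruited, while the information sessions and list scanning are described as still to come. The more natural reading is that allocation came first and the criteria and selection follow.

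**Step 2: what separates selection from arm.**
- Screening of every parent against the criteria keeps ineligible parents out. It does not govern which eligible parents are put forward, and the criteria themselves are still open.
- Procedure and Materials calls the scanning of lists transparent. That is neither a sampling rule nor concealment.
- No consecutive or exhaustive listing is described, and names can be added throughout.

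**Step 3: consent rate.** Let s be the share of eligible parents whom clinicians select and approach, i the share of those who say they are interested, and c the share of the database who consent. The documents give none of these. Assume c = 0.80, i = 0.30 to 0.60 and s = 0.10 to 1.00.
- Rate in the database: c = 80%.
- Rate among approached parents: i × c = 0.30 × 0.80 = 24% to 0.60 × 0.80 = 48%.
- Rate among all eligible parents, if no unselected parent would have consented: s × i × c = 0.10 × 0.30 × 0.80 = 2.4% to 1.00 × 0.60 × 0.80 = 48%.

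The third line is a lower bound for each s. If unselected parents would respond like the selected ones, the rate among all eligible parents returns to i × c. The second line needs no assumption about selection: counting from the database rather than from parents approached overstates consent by a factor of 1/i, here 1/0.60 = 1.7 to 1/0.30 = 3.3. Self-referrals enter the numerator with no approached group behind them.

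**Step 4: arm comparison.** If a fraction q of one arm's parents are chosen who score d SD higher than those otherwise enrolled, the arm mean moves by q × d. With assumed q = 0.1 to 0.3 and d = 0.5 to 1, the shift is 0.1 × 0.5 = 0.05 SD to 0.3 × 1 = 0.30 SD. Spread evenly, 90 parents over 18 sites is 5 per site, so a fraction of 0.2 is one parent per site. This shows sensitivity only; nothing in the documents estimates q or d.

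**The case against.** The strongest reply is that much of the alarming version is not in the text.

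- A reader might infer that clinicians know their site's arm when they scan their lists. The article does not say so, and a condensed article's silence on concealment does not show that there is none.
- A reader might infer that each site sets its own criteria. The article speaks of an information session without saying whether it is joint or held per site. Different criteria by site are possible, not stated.
- A reader might conclude that no valid consent rate can result. That goes too far: a rate among invited parents can be computed, all parents are screened, and counts of parents listed or approached may be in the full protocol, which is not shown.
- A reader might say that randomisation is undone. This is too strong for a mainly descriptive pilot that takes the main questionnaires at baseline, where imbalance on those scores would show, and that also recruits by routes that bypass clinicians.
- The Results section does not say that the 11 recruited sites are 11 of the 18 identified, so a count of 7 still to join is an inference.

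All of this stands as a limit on the claim. It does not remove what the article does state: allocation reported as done, criteria still open, discretionary choice by clinicians, and the same route used in Stage 2. Baseline scores also cannot reveal imbalance in features that they do not measure, such as motivation to use an app.

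**Conclusion.** The point holds as a risk built into the stated procedure. Parents are chosen by clinicians, on criteria not yet final, after the sites' arms were reportedly fixed, and no described step makes that choice independent of arm. Whether the arms will in fact differ cannot be judged from the document.

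The effect on the consent rate is clearer. A rate taken from the database of selected and interested parents describes invited parents, not all approached or eligible parents. Under the assumed interest shares it would be 1.7 to 3.3 times the rate among approached parents. The size of any bias in the arm comparison is unknown; 0.05 to 0.30 SD is an illustration. The conclusion rests on reading allocation as complete and on the recruitment route as described, not on the absence of a screening log. It should be corrected before more Stage 2 parents enrol, because the planning figures for the RCT depend on it.

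**What to change.** 1. Lock one common set of inclusion and exclusion criteria for all sites before further Stage 2 enrolment. Information sessions may advise on logistics but not alter the criteria.
2. Have clinicians list all parents who meet those criteria and invite from that list, logging a reason for each parent left out. At sites not yet recruited, complete the list before the arm is disclosed.
3. Report the consent rate with approached eligible parents as the denominator, by site and arm, and report self-referrals separately.

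The cost is protocol wording, a simple log at each site and some loss of clinician discretion. Sites already enrolling can apply items 1 and 3 at once. Where the arm is already known, item 2 still gives a defined list but not concealment, and the report should say so. The article should also state whether clinicians know the arm when selecting, and whether the sessions are joint or per site.
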